## 12.2 SAMPLE SIZE DETERMINATION

- **Assumptions:**

- Mean Quality of life utility scores of control group = 0.87 [SD=0.17] (Jyani et al., 2023)
- Effect size: Based on anticipated (clinically meaningful) improvement of 10% in HRQoL scores ([name] et al., 2025)
- Power: 90%
- Significance level: 0.05
- Intra-cluster correlation: 0.24 ([name] et al., 2023)
- Attrition rate: 25%

- **Calculation Methodology:** The following steps were used for the calculation of sample size

1. Effect size calculation

Effect size is the standardized mean difference between the control and intervention groups: calculated using the following formula,

$$Effect\ Size\ (Cohen's\ d) = \frac{Mean\ difference\ (Improvement)}{SD}$$

2. Sample size for two sample t-tests

The formula to calculate the sample size for a two-sample t-test is based on the following

$$n = \frac{(Z_{1-\alpha/2} + Z_{1-\beta})^2}{d^2} * \frac{2(SD)^2}{Effect\ size}$$

Where:

- $Z_{1-\alpha/2}$  is the critical value for a two-tailed test at the significance level  $\alpha$ .
- $Z_{1-\beta}$  is the critical value corresponding to the desired power  $(1-\beta)$ .
- $d$  is the effect size.
- $SD$  is the standard deviation

The `pwr.t.test()` function in R is used to perform this calculation, which outputs the required sample size for each arm of the trial assuming a simple t-test.

### 3. Design Effect Adjustment for Clustering

In cluster randomized trials, the design effect is used to adjust for the fact that individuals within the same cluster are likely to be more similar to each other than to individuals in other clusters. The design effect (DE) is calculated as:

$$\text{Design Effect (DE)} = 1 + (m - 1) * ICC$$

$$n_{adjusted} = n * DE$$

Where:

- $m$  is the number of participants per cluster.
- $ICC$  is the intraclass correlation coefficient.

### 4. Adjustment for Attrition:

Finally, the sample size is adjusted for expected attrition (dropout) by dividing the adjusted sample size by the retention rate:

$$n_{final} = \frac{n_{adjusted}}{1 - \text{Attrition Rate}}$$

### 5. Sample Size per Cluster

The final sample size per cluster is calculated by dividing the adjusted and attrition-corrected sample size by the number of clusters:

$$\text{Sample size per cluster} = \frac{n_{final}}{\text{Number of clusters}}$$

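### Section 12.2 states 90% power, but its written steps do not support it: the step 2 formula is misprinted, and the cluster steps hide a floor of 20 to 21 PHCs per arm

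*Protocol*

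**What the plan says.** Section 12.2 of the protocol lists the inputs and then five calculation steps. The inputs are:

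- "Mean Quality of life utility scores of control group = 0.87 [SD=0.17", with the bracket closing after the SD;
- "Effect size: Based on anticipated (clinically meaningful) improvement of 10% in HRQoL scores";
- power of 90%, "Significance level: 0.05", two-sided because the first z value "is the critical value for a two-tailed test at the significance level";
- "Intra-cluster correlation: 0.24";
- attrition of 25%.

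Step 2 prints a formula for n that divides the squared sum of z values by d squared, then multiplies by twice the SD squared over the effect size. The notes define d as that same effect size. The text adds that pwr.t.test() in R does the calculation and returns n for each arm.

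Step 3 multiplies n by a design effect of 1 + (m - 1) x ICC, where m "is the number of participants per cluster". Step 4 divides by the retention rate. Step 5 reads: "The final sample size per cluster is calculated by dividing the adjusted and attrition-corrected sample size by the number of clusters".

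The section ends there. It gives no n, design effect, m, number of PHCs or total N, and the rest of the protocol text does not supply the number of PHCs or m.

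**The concern.** There are two separate faults.

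First, step 2 as printed is not the two-sample formula. Because d is already standardised, the SD should not appear again, and the effect size should enter squared, not cubed.

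Second, cluster size goes into step 3 and comes out of step 5 with nothing tying the two together. With a high ICC this matters. Beyond a point, extra participants in the same PHC add almost no information, so the number of PHCs caps the power. A one-pass calculation from a guessed m cannot reveal that cap, and it reports 90% whether or not the design can deliver it.

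The PHCs all lie in one city, and enrolling more people per PHC later cannot repair too few clusters. The check therefore has to be made on the number of PHCs.

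**Working it through.** **Inputs (section 12.2).** Control mean 0.87, SD 0.17, gain 10%, power 90%, two-sided alpha 0.05, ICC 0.24, attrition 25%. Assumed here: 1:1 allocation of PHCs, 10% read as relative (0.10 x 0.87 = 0.087), and no credit for baseline adjustment.

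**The plan's own figure.** The only result stated is 90% power. It cannot be reproduced, because no number of PHCs or cluster size is given to compute it from.

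**Step 2.**
- d = 0.087 / 0.17 = 0.5118, d squared = 0.2619.
- (1.960 + 1.2816) squared = 10.507.
- Formula as printed: 10.507 / 0.2619 x (2 x 0.0289) / 0.5118 = 4.53, so 5 per arm.
- Standard formula: 2 x 10.507 / 0.2619 = 80.24, so 81 per arm.
- Two-sample t test, which is what pwr.t.test computes: 81.21, so 82 per arm.

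**Steps 3 to 5 run once.** Take m = 20 in step 3 as an illustration. The design effect is 1 + 19 x 0.24 = 5.56; 81.21 x 5.56 = 451.5; and 451.5 / 0.75 = 602 enrolled per arm.
- With 23 PHCs per arm, step 5 gives 602 / 23 = 26.2 enrolled, or 19.6 analysed. That matches the m assumed.
- With 10 PHCs per arm, step 5 gives 60 enrolled, or 45 analysed. That does not match, and nothing in the steps flags it.

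**Steps 3 to 5 solved consistently.** With k PHCs per arm and m analysed per PHC:

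k x m = n x (1 + (m - 1) x ICC), so m = n(1 - ICC) / (k - n x ICC).

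A positive m exists only if k > n x ICC:
- n = 80.24: 19.26.
- n = 81.21: 19.49.

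Either way, at least 20 PHCs per arm are needed. This treats m as the analysed number. If m in step 3 were the enrolled number, as the step 5 output is, the floor would be 19.26 / 0.75 = 25.7 to 19.49 / 0.75 = 26.0, so 26 PHCs per arm.

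**Maximum power with unlimited m.** The standard error tends to SD x sqrt(2 x ICC / k). For k = 10 it is 0.17 x sqrt(0.048) = 0.03725; 0.087 / 0.03725 = 2.336; 2.336 - 1.960 = 0.376, which gives 65%.

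| PHCs per arm | Normal | t on 2k-2 df |
|---|---|---|
| 10 | 64.7% | 59.9% |
| 15 | 81.6% | 78.9% |
| 19 | 89.6% | 88.0% |
| 20 | 91.0% | 89.6% |
| 21 | 92.3% | 91.0% |

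The floor is 20 by the normal approximation and 21 by the t test.

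**Analysed m for 90% power, t on 2k-2 df**, rounded up, then divided by 0.75:

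| k per arm | Analysed m | Enrolled per PHC | Total enrolled (2k PHCs) |
|---|---|---|---|
| 21 | 84 | 112 | 4,704 |
| 22 | 36 | 48 | 2,112 |
| 25 | 13 | 18 | 900 |

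The degrees of freedom matter. The closed formula with n = 81.21 gives m = 121 at k = 20 and m = 25 at k = 22. On the t basis these reach only 88.8% and 89.0%.

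**If 10% means 0.10 absolute.** d = 0.588 and n = 60.7 (normal) or 61.7 (t test), so n x ICC = 14.6 to 14.8. The floor is 15 by the normal approximation and 16 by the t test, where the cap is 88.8% at 15 PHCs and 90.8% at 16.

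**The case against.** Three stronger conclusions are tempting, and the protocol does not support them.

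- A reader might infer that the trial was sized on 5 per arm. Section 12.2 says directly after the formula that pwr.t.test() was used, and no figure near 5 appears anywhere. The formula is most likely misprinted, not misapplied.
- A reader might infer that the trial is underpowered. The protocol gives no number of PHCs, so nothing shows a shortfall. The 10-PHC figures are illustrative only. With matching values, such as m = 20 and 23 PHCs per arm, the same steps return a coherent design with about 91% power (normal) or 89.6% (t). The steps fail to guard against a mismatch; they do not create one.
- A reader might infer that step 5 divides a per-arm n by the total number of clusters and so halves the cluster size. Since n is per arm, clusters per arm is the natural reading. The wording is loose, but no error is shown.

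The floor is also conditional. The endpoint is a change with a baseline measurement (section 3), and mixed-effects models are planned (section 12.4.1). Baseline adjustment could reduce the number of PHCs needed. That objection stands as a limit on the figure of 20 or 21. It does not rescue the 90%, because section 12.2 takes no such credit. Nor does it repair the printed formula or link m in step 3 to the output of step 5.

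**Conclusion.** The point holds as a fault in the written method. The step 2 formula is wrong as printed, by about 18-fold (81.21 / 4.53) against the function named beside it. The cluster steps do not enforce agreement between the cluster size assumed and the one returned. The 90% is therefore tied to no design that can be checked, and on the protocol's own inputs it is out of reach below 20 PHCs per arm (normal) or 21 (t).

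That floor rests on 1:1 allocation, a relative gain of 0.087, an unadjusted comparison, and m counted as analysed participants. Reading the gain as 0.10 absolute lowers it to 15 or 16. Whether this trial meets the floor cannot be told from the protocol.

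**What to change.** 1. Correct step 2 to n = 2(z_{1-alpha/2} + z_{1-beta})^2 / d^2 per arm, and say whether 10% is relative or absolute.
2. Replace steps 3 to 5 by one calculation: fix k, the actual number of PHCs per arm, and solve for the analysed m that gives 90% power, using t with 2k-2 degrees of freedom throughout. Divide m by 0.75 for enrolment.
3. Say that any division by clusters means clusters per arm, and that m in the design effect is the analysed number.
4. State k per arm, enrolled and analysed m, the design effect and total N.
5. If the available PHCs fall below the floor, replace the 90% by the power they deliver. If credit is taken for baseline adjustment, state the assumed correlation and show its effect.

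The cost is one recalculation and a revised paragraph. The correction itself requires no extra participants, though the stated power may fall once the number of PHCs is entered.

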### 12.3 POPULATIONS FOR ANALYSES

The analysis will use the Intention-to-Treat (ITT) approach, which includes all randomized participants, regardless of their level of adherence to the intervention or any withdrawals from the study. This method preserves the benefits of randomization, allowing an assessment of the intervention's effectiveness under real-world conditions by accounting for typical variations in participant behaviour and engagement. By including all randomized individuals, the ITT analysis offers a realistic estimate of the intervention's impact on the general population represented in the study.

### 12.4 STATISTICAL ANALYSES

#### 12.4.1 GENERAL APPROACH:

The study will ensure secure data storage with controlled access to maintain participant confidentiality. Data management procedures will be implemented to ensure data accuracy, completeness, and integrity, with regular quality checks to address any discrepancies or missing data. The data analysts will be blinded to the groups. Descriptive analysis of the trial data will summarize participant characteristics, including demographics, baseline health status, and distribution of chronic conditions, with means, standard deviations, medians, and frequencies calculated as appropriate. Data will be analyzed (intention to treat) using appropriate statistical methods, such as mixed-effects models to account for clustering. We will compare the outcomes between the intervention and control groups to assess the effectiveness of the Multi-FrAME intervention, adjusting for clustering. Further, we will conduct subgroup analyses to explore potential moderators (e.g., age, gender) or mediators (e.g., adherence to the intervention) of the intervention effect.

#### 12.4.2 ANALYSIS OF THE PRIMARY ENDPOINT(S)

- **Outcome:** Health-related quality of life measured by EQ-5D-5L.
- **Method:** The primary outcome of this study is health-related quality of life, assessed using the EQ-5D-5L scale. The EQ-5D-5L instrument measures quality of life across five domains

(mobility, self-care, usual activities, pain/discomfort, and anxiety/depression), with each domain scored on five levels of severity. An overall utility score for quality of life will be calculated by mapping these responses to a single index value, facilitating comparison across participants. This index value is a continuous interval measure that allows for nuanced assessment of changes in health status. Primary outcome measures will be compared between the intervention and control groups using appropriate statistical tests based on the nature of the outcome variables (e.g., t-tests, chi-square tests, or non-parametric tests) to assess differences in outcomes. We will use adjusted Odds ratios arrived at using mixed effect models to calculate effect sizes and corresponding confidence intervals to quantify the magnitude of intervention effects.

---

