## 6.4 MEASURES TO MINIMIZE BIAS

### Randomization and Blinding

- **Randomization:** PHCs will be randomized to intervention or control groups to reduce selection bias.

- **Observer Blinding:** Outcomes will be assessed by blinded evaluators to minimize measurement bias.

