#### 12.4.3 ANALYSIS OF THE SECONDARY ENDPOINT(S)

- **Outcomes:** Frailty progression, ADL/IADL scores, healthcare utilization, costs, patient satisfaction, medication adherence, mortality, along with all the laboratory measurements.
- **Method:** Each secondary outcome will be clearly defined and analyzed to evaluate the broader impacts of the intervention on participants' health and well-being. Frailty progression will be assessed through a frailty score as a continuous measure. Functional limitations will include work-limiting conditions, mobility, Activities of Daily Living (ADL), and Instrumental Activities of Daily Living (IADL), scored on an ordinal scale, using categorical measures (e.g., "able" vs. "unable"). Health care utilization will be measured by tracking healthcare events (e.g., visits, hospitalizations) in a binary or categorical format, while health care expenditure will be recorded as a continuous variable, capturing both mean and median expenditures. Medical adherence will be represented as a percentage, indicating the proportion of prescribed medications participants adhered to. Statistical comparisons of these secondary outcomes between the intervention and control groups will employ appropriate tests for each outcome variable type to assess differences. Mixed-effect models will calculate adjusted odds ratios to determine effect sizes, with corresponding confidence intervals to quantify the intervention's impact.

---

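### Section 12.4.2 offers, as examples, tests that ignore PHC clustering for the primary comparison, which contradicts section 12.4.1 and leaves the deciding analysis unfixed

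*Protocol*

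**What the plan says.** - **Unit of randomisation.** Section 6.4: "PHCs will be randomized to intervention or control groups to reduce selection bias".
- **Planning assumption.** Section 12.2 lists "Intra-cluster correlation: 0.24" and multiplies the individual-level sample size by a design effect of 1 + (m − 1) × ICC. Neither m nor the number of PHCs is given.
- **Primary outcome scale.** Section 12.4.2, on the EQ-5D-5L index: "This index value is a continuous interval measure that allows for nuanced assessment of changes in health status".
- **Primary comparison.** Section 12.4.2 says the arms will be compared with tests suited to the type of variable, and gives as examples "e.g., t-tests, chi-square tests, or non-parametric tests) to assess differences in outcomes".
- **Primary effect size.** The next sentence of section 12.4.2: "We will use adjusted Odds ratios arrived at using mixed effect models to calculate effect sizes and corresponding confidence intervals".
- **General approach.** Section 12.4.1 says the data will be analysed "using appropriate statistical methods, such as mixed-effects models to account for clustering". Its following sentence says, without condition, that outcomes will be compared between arms with adjustment for clustering.
- **Elsewhere.** Section 12.4.5 again gives mixed-effects models as the example for comparing outcomes between arms. Section 12.4.3 says that comparisons of the secondary outcomes "will employ appropriate tests for each outcome variable type to assess differences", and that mixed models supply adjusted odds ratios.

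**The concern.** Section 12.4.2 governs the primary endpoint, and it splits the analysis. The test of difference comes from one family of methods, the estimate and interval from another. Every test it names for the difference assumes independent observations as normally run, so its p-value would not hold the 5% level in a trial that randomises PHCs. That p-value could also disagree with a mixed-model interval reported beside it, and the protocol does not say which one counts.

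The mixed-model sentence does not settle the matter. It promises odds ratios, which require a binary or ordinal outcome, and no dichotomisation of the index is described. Of the methods named in section 12.4.2, only the t-test and the non-parametric tests can be applied to the index as defined. An analyst who followed that section literally would report an unadjusted p-value as the primary result.

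**Working it through.** **Inputs.** ICC 0.24 and two-sided alpha 0.05 come from section 12.2. The design-effect formula comes from the same section. The number analysed per PHC (m) and the number of PHCs are not stated, so both are assumed over a range. The protocol states no error rate for the primary test, so there is no figure of its own to reproduce.

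**Step 1: design effect.** DE = 1 + (m − 1) × 0.24. For example, at m = 20, DE = 1 + 19 × 0.24 = 5.56.

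**Step 2: effect on an unadjusted test.** The unadjusted standard error is too small by a factor of √DE, so under the null hypothesis the test statistic has standard deviation √DE instead of 1. The true two-sided error of a nominal 5% test is

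2 × [1 − Φ(1.96 / √DE)].

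At m = 20: √5.56 = 2.36; 1.96 / 2.36 = 0.83; 2 × [1 − Φ(0.83)] = 0.41.

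| m per PHC (assumed) | DE | True type I error |
|---|---|---|
| 5 | 1.96 | 0.16 |
| 10 | 3.16 | 0.27 |
| 20 | 5.56 | 0.41 |
| 30 | 7.96 | 0.49 |
| 40 | 10.36 | 0.54 |
| 50 | 12.76 | 0.58 |

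The rate passes one half when 1.96 / √DE falls below 0.6745. That requires DE > 8.44, which is first met at m = 33.

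**Step 3: sensitivity to the ICC.** If the ICC were 0.05 instead, m = 20 gives DE = 1 + 19 × 0.05 = 1.95 and a type I error of 0.16.

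**Step 4: simulation under the null.** Normal outcomes, ICC 0.24, equal PHC sizes; 4,000 trials per setting (1,500 for Mann-Whitney).

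| PHCs per arm | m | Individual-level t-test | Mann-Whitney | t-test on PHC means |
|---|---|---|---|---|
| 10 | 10 | 0.27 | 0.26 | 0.049 |
| 5 | 20 | 0.40 | 0.40 | 0.042 |
| 10 | 20 | 0.40 | 0.39 | 0.046 |
| 15 | 20 | 0.41 | 0.42 | 0.050 |
| 20 | 20 | 0.39 | 0.37 | 0.051 |
| 10 | 40 | 0.55 | 0.56 | 0.051 |

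The simulation agrees with the formula. Adding PHCs does not cure the inflation. An analysis that respects the PHC stays at or slightly below 5%.

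**The case against.** The strongest reply is that the protocol plainly intends to account for clustering. Section 12.4.1 commits the between-arm comparison to adjustment without condition and leaves only the choice of method as an example. Section 12.4.5 cites mixed models, section 12.4.2 takes its own intervals from mixed models, and the sample size carries a design effect. The tests in section 12.4.2 are introduced as examples and read like a generic list; chi-square appears although the index is continuous. A t-test on PHC summaries would be valid.

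Much of this stands. A reader might infer from section 12.4.2 that the primary analysis has been fixed as an individual-level test and that a false positive is therefore very likely. The documents do not support that. The list is not binding, section 12.4.1 points the other way, and the size of the error depends on a PHC size the protocol does not give; it exceeds one half only from 33 participants per PHC. Nor does section 12.4.3 name any unadjusted test. Its wording is vague, and a statistical analysis plan could settle it.

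What the reply does not remove is the conflict. Section 12.4.2 never mentions PHC summaries, all its examples are of a kind that ignores clustering as normally run, and its one clustering-aware sentence prescribes an effect measure that does not fit the outcome. This is not detail deferred to an analysis plan: one written to follow the protocol would inherit the contradiction.

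**Conclusion.** The point holds as an internal contradiction over the deciding primary analysis, with unsuitable tests named in the section that governs the primary endpoint. It does not show that the trial will be analysed without regard to clustering.

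The consequence is conditional. If the unadjusted p-value decided the trial, the type I error at the plan's own ICC would be about 3 to 12 times nominal over 5 to 50 participants per PHC (0.16 / 0.05 = 3.2; 0.58 / 0.05 = 11.7). These figures assume equal PHC sizes, the stated ICC and the assumed m. Even at an ICC of 0.05, 20 participants per PHC would give about three times the nominal rate. Because the validity of the primary conclusion turns on which sentence is followed, this should be corrected before analysis.

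**What to change.** In section 12.4.2:
- Delete the list of t-tests, chi-square and non-parametric tests, or limit it to descriptive use.
- Replace the odds-ratio sentence; otherwise the section would still prescribe an effect measure that does not fit the index.
- State that the primary p-value, the estimate (adjusted mean difference in EQ-5D-5L index) and its 95% CI all come from one analysis that accounts for PHC. This can be a linear mixed model with a random intercept for PHC and a small-sample correction, or a t-test on PHC-level summaries if PHCs are few.

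In section 12.4.3, add that the tests for secondary outcomes also account for clustering.

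The cost is wording only. P-values and intervals will be less favourable than unadjusted ones. The sample-size method in section 12.2 already includes a design effect, so this change does not by itself call for more participants.

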### 3 OBJECTIVES AND ENDPOINTS

The primary healthcare intervention package (Multi-FrAME) is expected to improve health outcomes for older adults with multimorbidity and frailty, including a reduction in frailty progression and enhanced functional ability. This will assess the following outcomes.

| Objectives                                                                                      | Endpoints                                                   | Justification For Endpoints                                                       | Putative Mechanisms Of Action                                   |
|-------------------------------------------------------------------------------------------------|-------------------------------------------------------------|-----------------------------------------------------------------------------------|-----------------------------------------------------------------|
| 3.1 PRIMARY OBJECTIVES                                                                          |                                                             |                                                                                   |                                                                 |
| Assess the effectiveness of the Multi-FrAME package in improving health-related quality of life | Change in EQ-5D-5L index scores at 0, 6, and 12 months      | EQ-5D-5L is validated for use in India and measures multiple dimensions of health | Comprehensive care improves physical, mental, and social health |
| 3.2 SECONDARY OBJECTIVES                                                                        |                                                             |                                                                                   |                                                                 |
| Evaluate improvement in frailty                                                                 | Change in frailty index scores (deficit accumulation model) | Reliable measure for frailty changes                                              | Nutritional support and physical activity reduce frailty        |
| Assess improvement in ADL/IADL                                                                  | Change in ADL/IADL scores using Lawton IADL Scale           | Validated measure for functional status                                           | Improved physical and cognitive functioning                     |

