### 9.1 ENDPOINT AND OTHER NON-SAFETY ASSESSMENTS

#### A. Primary Endpoint:

- **Health-Related Quality of Life:**

- **Tool:** EQ-5D-5L Index (EuroQol Group, 1990)
- **Assessment:** Administered at 0, 6, and 12 months. Investigator administered.

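### The primary effect is to be reported as an odds ratio, although the EQ-5D-5L index is continuous and the trial is sized on a mean difference

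*Protocol*

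**What the plan says.** Protocol section 12.4.2 maps the five EQ-5D-5L domains to a single utility value and states: "This index value is a continuous interval measure". It then offers an open list of tests for comparing the arms ("e.g., t-tests, chi-square tests, or non-parametric tests) to assess differences in outcomes"). The paragraph ends by fixing the effect measure: "We will use adjusted Odds ratios arrived at using mixed effect models to calculate effect sizes and corresponding confidence intervals".

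Section 12.2 sizes the trial from a control mean of 0.87 with SD 0.17 and an "anticipated (clinically meaningful) improvement of 10% in HRQoL scores". It defines the effect size as the mean difference divided by the SD and uses a two-sample t-test.

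The table in section 3 gives the primary endpoint as "Change in EQ-5D-5L index scores at 0, 6, and 12 months". Section 9.1 confirms that the instrument is "Administered at 0, 6, and 12 months".

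Section 12.4.3 treats the frailty score and healthcare expenditure as continuous, but the only effect measure it names is again the odds ratio: "Mixed-effect models will calculate adjusted odds ratios to determine effect sizes".

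**The concern.** An odds ratio needs a binary or ordinal outcome. The index is described as neither, so the primary estimate cannot be produced without a transformation that the protocol does not state. Detail left to a statistical analysis plan would be no finding, but here the protocol itself fixes an effect measure, and it does not suit the outcome. An analysis plan that followed it would inherit the problem, and one that used a mean difference would contradict the protocol.

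Two things are at stake. The headline result would be on a scale that cannot be set against the difference the trial was designed to detect. And if an odds ratio were obtained by cutting the index, both the estimate and the power would depend on where the cut fell, which nothing in the protocol settles in advance.

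**Working it through.** **Planned effect.** Inputs from section 12.2: control mean 0.87, SD 0.17, improvement 10%, power 90%, two-sided level 0.05, ICC 0.24. Reading the 10% as relative:

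- difference = 0.10 × 0.87 = 0.087 index points
- d = 0.087 / 0.17 = 0.512
- n per arm before clustering and attrition = 2 × (1.960 + 1.2816)² / 0.512² ≈ 80.2, so 81 (82 with the t-test)

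The protocol prints no resulting total, number of clusters or cluster size, so there is no stated figure to reproduce. All of this arithmetic is on the mean-difference scale.

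**What odds ratio would match the planned effect?** It depends on the cut. Assume a normal outcome, means 0.87 and 0.957, SD 0.17. The cut-points are assumptions, because the protocol gives none.

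- Cut at 0.87: 50.0% against 69.6% above the cut; odds ratio = (0.696/0.304) / (0.500/0.500) = 2.29
- Cut at 0.70: 84.13% against 93.47%; odds ratio = (0.9347/0.0653) / (0.8413/0.1587) = 2.70

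The same 0.087-point difference gives different odds ratios, so an odds ratio alone cannot show whether 0.087 was reached.

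**Power if the index were split at the median.** Dichotomising loses information within a person, but it also lowers the ICC, so both must be counted.

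- Binary ICC at a median cut of normal data = (2/π) × arcsin(0.24) = 0.154
- Relative efficiency = (2/π) × [1 + 0.24(m − 1)] / [1 + 0.154(m − 1)]
- Power = Φ(√efficiency × (1.960 + 1.2816) − 1.960), for a design with 90% power on the continuous index

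| Assumed cluster size m | Design effect, continuous | Design effect, binary | Relative efficiency | Power |
|---|---|---|---|---|
| 10 | 3.16 | 2.39 | 0.84 | 84.5% |
| 20 | 5.56 | 3.93 | 0.90 | 86.8% |
| 50 | 12.76 | 8.56 | 0.95 | 88.4% |

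**An off-centre cut costs more.** For the cut at 0.70, the bivariate normal distribution with correlation 0.24 gives binary ICCs of 0.118 (control) and 0.082 (intervention). For m = 10:

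- n per arm = 80.2 × 3.16 ≈ 254
- variance of the difference = [0.1335 × (1 + 9 × 0.118) + 0.0610 × (1 + 9 × 0.082)] / 254 ≈ 0.00150, SE ≈ 0.0387
- power ≈ Φ(0.0934/0.0387 − 1.960) ≈ 67%

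The same steps with m = 20 (n = 446) and m = 50 (n = 1,024) give about 73% and 77%.

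**Section 12.4.3.** Setting the outcomes beside the effect measure, odds ratios suit the outcomes recorded as binary or ordinal (utilization events, able or unable function, death). They do not suit the frailty score or expenditure, which the section describes as continuous.

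**The case against.** The best reply is that the odds-ratio sentence governs only the effect size and its interval. The sentence before it chooses the test by the type of outcome and lists t-tests, so the arms could still be compared on means, in line with section 12.2. That stands: a loss of power for the test itself does not follow from the text. It does not rescue the estimate, because the sentence on effect size names only the odds ratio.

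Three stronger readings are tempting, and the documents do not support them.

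- *A reader might infer that the index will be dichotomised.* No section says so. An odds ratio could come from an ordinal model, which needs no cut-point and loses little: efficiency about 3/π = 0.955 under normality, or about 89% power with independent data. The power figures for a split are therefore conditional.
- *A reader might apply the efficiency 2/π = 0.64 for independent observations and infer that power falls to about 73% under a median split.* That ignores clustering. At ICC 0.24 the binary outcome has a smaller design effect, and the loss from a median split is about 2 to 6 percentage points.
- *A reader might infer that the baseline index goes unused.* Section 3 defines the endpoint as change, which is computed from baseline, and section 12.4.2 says the estimates are adjusted without listing covariates. A covariate list may sit in an analysis plan that is not shown. What can be said is that section 12.4.2 does not tie its analysis to change. Precision gains of the form 1 − r² cannot be claimed either: no r is given, and in a clustered design the gain also depends on the correlation at cluster level.

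It is also fair that the odds-ratio sentence in section 12.4.3 covers a mixed list. The objection there is confined to the continuous outcomes.

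**Conclusion.** The point holds as a contradiction within the protocol. Section 12.4.2 fixes an odds ratio as the only effect measure for an index it calls continuous, while section 12.2 sizes the trial on a mean difference of 0.087 points (d = 0.51, with the 10% read as relative). As written, the primary estimate cannot be compared with the planned difference. This conclusion rests on the text alone and needs no assumption about cut-points.

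The statistical cost is conditional. If the odds ratio came from a median split, 90% power would become about 84 to 88%; a cut at 0.70 would leave about 67 to 77%. These figures assume normal data, ICC 0.24 and cluster sizes of 10 to 50. They are illustrative, since a utility index capped at 1 is likely to be skewed. The mismatch concerns the trial's headline result and should be corrected before the data are analysed.

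**What to change.** In section 12.4.2, replace the odds-ratio sentence with wording such as: *The effect of the intervention is the adjusted mean difference, with 95% confidence interval, in the EQ-5D-5L index between arms, estimated from a linear mixed model with arm and baseline index as fixed effects and a random intercept for PHC.* Entering the baseline index brings the analysis into line with the change endpoint in section 3.

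The sponsor should state which follow-up time, 6 or 12 months, is primary and how the other enters the analysis.

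In section 12.4.3, use mean differences for the continuous outcomes, including the frailty score and expenditure, and keep odds ratios for the binary or ordinal ones.

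The cost is a short amendment to the text and one design decision, the primary time point. The index is already collected at 0, 6 and 12 months, so no new data are needed, and the sample size calculation already uses the mean-difference scale.
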